Despite these grim statistics, randomized controlled trials of two interventions (one clinical and one behavioral) hold promise for improving bowel preparation and adenoma detection. Irrespective of the bowel preparation [16], *split-dosing* can improve the adequacy of bowel preparation by 10 percentage points (*p* < 0.0001) and adenoma detection by six percentage points (*p* < 0.001) and is more highly accepted [17] by patients compared to taking a full dose on the same day [18–20]. In addition, an almost fourfold improvement in adequacy of bowel preparation has been found among patients who receive *low-literacy education* compared to education written for 6th grade or higher [21]. However, written instructions are more effective when combined with verbal instructions [18, 22], signaling the importance of confirming patient understanding of bowel preparation instructions. Representing a third evidence-based practice (EBP) for improving bowel preparation, *teach-back* is the practice of reviewing instructions with patients, ensuring that patients can repeat key points (i.e., teach back), and addressing any barriers to completion of instructions. Both low-literacy education and teach-back are in accordance with the Agency for Healthcare Research and Quality’s and the National Quality Council’s recommendation for using universal precautions to improve health literacy in all patients.

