### Settings and subjects

This study will be conducted with a convenience sample of six endoscopy settings. Our study is highly pragmatic with regard to eligibility. We will invite all 70 physicians that perform outpatient colonoscopy, regardless of their specialty (i.e., gastroenterology, surgery), and all of their staff that provide bowel preparation education to patients before outpatient colonoscopy. All patients scheduled for outpatient colonoscopy will be included, regardless of whether they are scheduled for a screening or diagnostic procedure. The PRECIS diagram illustrated in Fig. 2 reflects the extent to which each indicator of the study was pragmatic versus explanatory. Table 1 explains the PRECIS diagram by providing an assessment of each PRECIS domain for this study [38]. Our strategic partners will facilitate recruitment of physicians by co-signing recruitment letters and, if recruitment challenges occurs, by sending emails, calling physicians, and introducing the study at department meetings. Based on previous experience with physician recruitment to studies, we anticipate participation from at least 80 % of eligible physicians (70*0.80 = 56 physicians) and that each physician will have at least two staff that provide education for bowel preparation (56*2 = *n* = 112 staff). To minimize the potential for diffusion of treatment to our comparison group, we will assign physicians’ staff either to usual care or to receive the implementation toolkit. Physicians in both study groups will receive education. Assignment will be based on baseline adequacy of bowel preparation, balance of patient units and structure of physician-staff relationship. Over 10,000 outpatient colonoscopies per year are performed in our sample. Overall, 23 % of patients are covered by Medicaid. We anticipate inclusion of more than 10,000 patients in the study (20,000 over 2 years*15/24 months observation = 12,500*0.80 minimum physician participation = 10,000 total, >600 per month).

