### Analysis

To assess change in clinical outcomes, we will use segmented regression analysis of interrupted time series data (SRAITSD). SRAITSD is an excellent analysis method for pragmatic studies because it minimizes threats to internal validity while maximizing external validity. For our application, individual patient outcomes are aggregated into proportion of adequate bowel preparation or proportion with adenoma detection in 2-week intervals, the time representing our unit of analysis. A sequence of the proportions over time generates time series data, with segments separated by two different interventions (i.e., comparative effectiveness and a replication study). The observation period for the time series analysis (Table 2) consists of three segments: baseline, comparative-effectiveness intervention, and replication study. Each segment is ~5 months in length. Two parameters define each segment of a time series: level and trend (see Additional file 1 for additional information on the analytic model) [42]. This model can be fit and tested using SAS software. We have a sufficient number of observations per segment (10 observations) and individual patient outcomes per observation (>100 units) for robust estimates of change in level and trend for outcomes [42, 43].

**Table 2 Tab2:** Interrupted time series study design—15-month observation period

Segments	Baseline			Comparative-effectiveness				Replication			
Group 1	O_1_	…	O_10_	X_1_	O_11_	…	O_20_	X_1_X_2_	O_21_	…	O_30_
Group 2	O_1_	…	O_10_	X_1_X_2_	O_11_	…	…	…	…	…	O_30_

*Note*: Each observation represents a 2-week interval. X1 = physician education, *X*2 = physician education plus staff training and support

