To test intervention effects in each group, we first examine the plots of 2-week proportions over time. Then, we will fit the model separately in each group. β2 and β3 are the change in level and in trend of outcome, respectively, due to the comparative-effectiveness intervention. β4 and β5, which only apply to group 1, are the change in level and in trend of outcome, respectively, due to the replication study beyond the comparative-effectiveness intervention. For each group, statistical significance of these changes can be tested using the ratios of these regression coefficients to their estimated standard errors (*p* value). Because our study adopts a parallel design, we can also examine the statistical significance of the difference in these changes across groups by computing the difference in the regression coefficients divided by a standard error of the coefficient difference (*p* value), which can be easily obtained from standard errors of the regression coefficients in two separate models. A statistically significant (*p* < 0.05) difference in change in the level of outcome for group 1 versus group 2 will inform us about the comparative effectiveness of the physician education versus the physician education *plus* implementation toolkit. Alternatively, a statistically significant (*p* < 0.05) difference in trends of outcomes for group 1 versus group 2 will inform us about potential threats to validity due to outside events or program drift that occurs when fidelity to implementation protocols weaken over time. Finally, a statistically significant (*p* < 0.05) difference in the level of outcomes for group 1 in segment 2 versus group 1 in segment 3 will inform us about the generalizability of the comparative-effectiveness study effects across endoscopy settings. In order to examine modifying intervention effect by insurance status, we will stratify our study subjects by Medicaid versus other insurance status. Therefore, we will have 4 time series—two groups by two insurance strata. These series have the same time definition and the same segments, so the regression coefficients have the same interpretation. We will fit SRAITSD to each of the 4 time series and compare the relevant regression coefficients between Medicaid versus other insurance.

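### The stated minimum of more than 100 patients per observation does not hold for the two Medicaid series (about 35–38 each), so the robustness statement should not extend to the insurance comparison

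*Protocol article*

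**What the plan says.** The Aim #1 Analysis section aggregates patient outcomes into proportions by two-week period; the note to Table 2 confirms that "Each observation represents a 2-week interval". Table 2 shows 30 observations per group in three segments of 10. The section then states that 10 observations per segment and the patients behind each are sufficient: "individual patient outcomes per observation (>100 units) for robust estimates of change in level and trend for outcomes".

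The closing lines of the same Analysis section turn to insurance status and define four series, two groups by two strata: "We will fit SRAITSD to each of the 4 time series and compare the relevant regression coefficients between Medicaid versus other insurance". No patient count is given for these series and the sufficiency statement is not qualified for them.

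The inputs stand under Settings and subjects. The sample is built as "20,000 over 2 years*15/24 months observation = 12,500*0.80 minimum physician participation = 10,000 total, >600 per month", and "Overall, 23 % of patients are covered by Medicaid". No allocation ratio is given; balance in patient numbers is one of the assignment criteria: "Assignment will be based on baseline adequacy of bowel preparation, balance of patient units and structure of physician-staff relationship".

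**The concern.** The sufficiency statement names a property, more than 100 patients behind each point, and a planned analysis a few lines later does not have it. With under a quarter of patients on Medicaid, a series restricted to them must be far thinner than the whole-group series.

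This matters because the insurance comparison is part (b) of Aim #1 and supplies the answer to the question of for whom the strategies work, which the Abstract and Discussion both promise. The Background calls Medicaid coverage one of the strongest risk factors for inadequate preparation. If the Medicaid series are presented as supporting robust estimates, a non-significant comparison is easily taken as evidence that the toolkit works equally well in both strata, when the data could not distinguish that from a large difference.

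**Working it through.** **Inputs from the protocol.** 10,000 patients, 15 months and 23% Medicaid (Settings and subjects); two-week intervals, 30 observations and three segments of 10 (Table 2); group 1 with six coefficients and group 2 with four, since β4 and β5 apply only to group 1 (Aim #1 Analysis); significance at p < 0.05, taken as two-sided.

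**Assumptions.** Groups about 1:1 with the same Medicaid share; constant binomial variance p(1−p)/n at each point; no autocorrelation, overdispersion or physician clustering. Baselines are not given for this sample. Adequacy is varied over 60–85%, with 70% as the central value because the Background says inadequate preparation can exceed 30%. Adenoma detection is varied over 20–30%, the range of the quality goals in the Background.

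**Step 1: reproduce the stated figures.** 20,000 × 15/24 × 0.80 = 10,000, and 10,000/15 = 667 per month, consistent with more than 600. Per group and interval: 10,000/30/2 = 167, or 10,000/32.5/2 = 154 if 15 calendar months are cut into two-week intervals. The stated minimum of 100 holds for the whole-group series.

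**Step 2: split by insurance.**

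| Series (each group) | 30 intervals | 32.5 intervals |
|---|---|---|
| All patients | 167 | 154 |
| Other insurance (× 0.77) | 128 | 118 |
| Medicaid (× 0.23) | 38 | 35 |

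At exactly 600 patients per month the 32.5-interval figures become 138, 107 and 32. No allocation could lift both Medicaid series above 100: all Medicaid patients from both groups together give only 2 × 35.4 = 71 to 2 × 38.3 = 77 per interval.

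**Step 3: precision of the level-change contrast.** From the design matrix, SE(β2) = k × √(p(1−p)/n), with k = 0.901 in group 1 and k = 0.749 or 0.808 in group 2, depending on how time after the interruption is coded. For the difference between groups, K = √(0.901² + 0.749²) = 1.172, or √(0.901² + 0.808²) = 1.210. The detectable difference at 80% power is (1.960 + 0.842) × SE = 2.802 × SE.

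Medicaid, adequacy, p = 0.70:
- n = 38.3: SD per point = √(0.21/38.3) = 7.40 points; SE = 1.172 × 7.40 = 8.7; detectable 24.3.
- n = 35.4: SD = 7.70 points; SE = 1.210 × 7.70 = 9.3; detectable 26.1.
- Power for a 10-point difference: about 19–21%.
- Over baselines of 60–85%, the detectable difference is about 19–28 points.

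Medicaid versus other insurance, difference in that contrast, with p = 0.70 for Medicaid and 0.80 for others:
- Lower end: SE = 1.172 × √(0.21/38.3 + 0.16/128.3) = 9.6 points; detectable 26.9.
- Upper end: SE = 1.210 × √(0.21/35.4 + 0.16/118.5) = 10.3 points; detectable 28.9.
- If the other-insurance baseline is also 70%, the upper end is just under 30.
- The 95% confidence interval would be about ±19 to ±20 points (1.96 × 9.6 to 1.96 × 10.3).

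For scale: from a 70% baseline, and with no change in the comparison group, a 24–26 point effect means adequacy of 94–96%.

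**Step 4: whole-group series, as a secondary benchmark.** The Background reports that split-dosing "can improve the adequacy of bowel preparation by 10 percentage points" and adenoma detection by six. Power is Φ(difference/SE − 1.96), over n = 154–167 and both codings:

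| Outcome, difference | Assumed baseline | Power |
|---|---|---|
| Adequacy, 10 points | 70% | 61–67% |
| Adequacy, 10 points | 80% | 73–79% |
| Adequacy, 10 points | 85% | 82–87% |
| Adenoma detection, 6 points | 20–30% | 27–38% |

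Autocorrelation lowers these figures. With AR(1) of 0.4 and K = 1.172's coding, the Medicaid detectable difference at 70% becomes about 28–29 points.

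**The case against.** The strongest reply is that the sentence is correct where it stands. It follows the description of the two group series in Table 2; both have well over 100 patients per observation, and so do the two other-insurance series. The insurance split comes later and repeats no count. All of that stands. A reader might infer that the figure is an arithmetic error throughout, and the documents do not support that: it reproduces for the whole groups and is merely carried, unqualified, into an analysis it does not fit.

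A reader might also infer that even the whole-group series cannot support a contrast of the size the protocol cites. That goes too far. For adequacy, a 10-point difference reaches 80% power at an 85% baseline and falls short at 70%, so the answer turns on an assumption. The shortfall for 6 points in adenoma detection is consistent across the baselines tried. But the protocol sets no power and no target for this contrast, robustness is not a power level, and the 10 and 6 points are background results for split-dosing alone. The toolkit also carries low-literacy education and teach-back, and the Background expects low-literacy material to be particularly helpful in Medicaid patients. Whether the added effect of the toolkit is smaller or larger than those figures cannot be settled from the document.

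Finally, nothing in the protocol says that a null insurance comparison will be read as no effect modification; it says only that coefficients will be compared. The risk lies in the robustness wording and is not a stated intention. None of these points raises the Medicaid counts.

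**Conclusion.** The concern holds for two of the four insurance series. On the protocol's own totals, each Medicaid observation rests on about 35–38 patients, a little over a third of the stated minimum, and no split between groups could bring both series up to it. The per-series counts depend on roughly equal groups and an equal Medicaid share.

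On binomial noise alone, the Medicaid group contrast in adequacy can detect about 24–26 points at a 70% baseline (19–28 over 60–85%), and the Medicaid-versus-other comparison about 27–29. Physician clustering, overdispersion and positive autocorrelation would be expected to widen these. A null insurance comparison would be close to uninformative. The whole-group power figures are context only: weak for 6 points in adenoma detection, dependent on the baseline for 10 points in adequacy. The primary whole-group analysis is not shown to be unsound, and the stated minimum is not wrong for it.

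**What to change.** 1. State the expected patients per observation for each kind of series: about 154–167 for a whole group, 118–128 for other insurance and 35–38 for Medicaid, with the assumed group ratio and Medicaid share.
2. Limit the sufficiency and robustness statement to the whole-group and other-insurance series, and say that the Medicaid series fall below the stated minimum.
3. Report the Medicaid-versus-other difference in level change with its 95% confidence interval, and state that a non-significant result will not be read as absence of effect modification.

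A single patient-level segmented model with insurance interactions, keeping the level and trend terms, is an option in place of four separate fits. Replacing the level change by a contrast of segment means would be more precise, but it changes the quantity estimated by giving up the separation of level and trend. It is a trade-off and is not required here.

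The cost is a few sentences and one reported interval from data already planned. No extra patients are needed; the price is a less favourable statement of what the insurance comparison can show.

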### Measures

The Center for Clinical Excellence at BJC will obtain all data required for aim #1 from clinical and administrative systems at the endoscopy settings. The primary outcomes for aim #1 are adoption of EBPs, adequacy of bowel preparation, and adenoma detection. We will measure adoption of the EBPs (i.e., split-dosing, use of low-literacy education materials, teach-back) using a structured survey administered to staff and patients at baseline and follow-up. Sample questions on adoption will assess whether staff asked patients to “take half of the bowel preparation medication” (the day before/the morning of the test), with response options including “No,” “Yes,” and “I don’t know/Not applicable.” Questions will also be asked about whether or not staff provided the recommended low-literacy paper instructions and whether or not staff asked patients to “repeat instructions for bowel preparation in their own words.” Both clinical outcomes (adequacy of bowel preparation, adenoma detection) are standard elements of colonoscopy reports [10], and earlier research suggests that these data are routinely recorded in electronic records [39]. Bowel preparation is commonly described using the Aronchick scale (Kappa ICC 0.77) [40] as excellent, good, fair, or poor. Excellent or good ratings are considered adequate [5, 39]. Excellent refers to no or minimal solid stool and only small amounts of clear fluid requiring suctioning. Good refers to no or minimal solid stool with large amounts of clear fluid requiring suctioning. Fair refers to collections of semisolid debris that are cleared with difficulty. Poor refers to solid or semisolid debris that cannot be effectively cleared. We will also capture information about factors that are associated with adequacy of bowel preparation and adenoma detection including characteristics of the patient (age, gender, type of insurance, co-morbid conditions (i.e., history of constipation, diabetes), body mass index, use of narcotic medications) [41], primary language [14], and procedure (i.e., physician specialty, type of bowel preparation, indication for procedure, date of procedure [8]).

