To assess the extent to which the implementation toolkit influenced adoption of EBPs over time, we will model adoption at follow-up as a function of study group assignment, controlling for the baseline measure of adoption. We will assess adoption for each EBP (i.e., split-dosing, low-literacy education, teach-back) separately and use separate statistical models for adoption measured from the perspective of the following: 1) staff, 2) physicians, and 3) patients. The regression coefficient for study group assignment will quantify the effect of different approaches on the outcome.

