### Analysis

If we find group-level effects, then we will dichotomize the readiness to change variables at mid-point (high, low) for the sample and analyze readiness to change at the physician-team level. We will examine the distribution of responses to the patient-experience survey for respondents overall and stratified by attendance. Our primary analysis for aim #2 will examine associations between each implementation and patient outcome and readiness to change using linear or logistic generalized estimating equations, depending on the distribution of the outcome, adjusted for patient and procedure characteristics. All analyses will be performed using SAS version 9.2. In addition, we will summarize data from aim #2 as six endoscopy setting case studies based on variability of clinical quality outcomes (aim #1) [46]. If we identify significant relationships between aspects of readiness to change and implementation, patient, or colonoscopy quality outcomes, then we will develop plans to analyze the patterns of these relations in a subsequent study that will be powered to address questions about pathways to readiness to change.

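### The adoption models state no allowance for clustering although the toolkit is assigned to a physician's staff as a group; fitted to individual survey respondents, they would understate the standard error of the toolkit effect

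*Protocol article*

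**What the plan says.** All references are to the protocol article.

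- **Outcome.** Under aim #1, Measures: "The primary outcomes for aim #1 are adoption of EBPs, adequacy of bowel preparation, and adenoma detection". Adoption is collected by a "structured survey administered to staff and patients at baseline and follow-up".
- **Assignment.** Under Settings and subjects: "we will assign physicians’ staff either to usual care or to receive the implementation toolkit". The criteria are characteristics of groups, not of respondents: "Assignment will be based on baseline adequacy of bowel preparation, balance of patient units and structure of physician-staff relationship". The article expects 56 physicians and at least two staff for each.
- **Model.** Under aim #1, Analysis: "we will model adoption at follow-up as a function of study group assignment, controlling for the baseline measure of adoption". Each practice is analysed separately, and the authors will "use separate statistical models for adoption measured from the perspective of the following: 1) staff, 2) physicians, and 3) patients". The reported effect is fixed too: "The regression coefficient for study group assignment will quantify the effect of different approaches on the outcome".
- **Correlated-data method.** It is named only under aim #2, Analysis, where associations with readiness to change are examined "using linear or logistic generalized estimating equations, depending on the distribution of the outcome". The outcomes listed for aim #2 are fidelity, dose, cost, experience, attendance, adherence and colonoscopy quality. Adoption is not among them.
- **Supplement.** Additional file 1 is cited for the time-series model only.

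**The concern.** Everyone who answers under one physician shares that physician's assignment. Staff of one physician follow that physician's choice of preparation and the same workflow, and patients of one team are taught by the same few people. Their answers on split-dosing, low-literacy materials and teach-back should therefore be positively correlated within a team.

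A regression on study group and baseline adoption that treats respondents as independent counts more information about a team-level effect than the data hold. The interval for the group coefficient is then too narrow. Ordinary variation between teams could be read as a toolkit effect on a primary outcome.

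This is separate from the segmented regression of 2-week proportions for bowel preparation and adenoma detection. That analysis uses other data and another model, and changing it would leave the adoption models as they are.

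**Working it through.** **The plan's own counts.** 70 × 0.80 = 56 physicians; 56 × 2 = 112 staff; 20,000 × 15/24 × 0.80 = 10,000 patients. All three reproduce. The article states no ICC, design effect or power for adoption.

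**Assumptions, because the article gives no figure.** ICC 0.1–0.5 for staff and 0.05–0.3 for patients; 5–20 patients surveyed per team; 28 teams per group; a two-sided 5% test. The article states p < 0.05 for the time series only.

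**Step 1: formula without the baseline term.** Design effect DE = 1 + (m − 1) × ICC. Actual error of a nominal 5% test = 2 × [1 − Φ(1.96/√DE)].

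| Model | m | ICC | DE | Actual error |
|---|---|---|---|---|
| Staff | 2 | 0.1 | 1.10 | 6.2% |
| Staff | 2 | 0.3 | 1.30 | 8.6% |
| Staff | 2 | 0.5 | 1.50 | 11.0% |
| Patients | 5 | 0.05 | 1.20 | 7.4% |
| Patients | 10 | 0.1 | 1.90 | 15.5% |
| Patients | 20 | 0.1 | 2.90 | 25.0% |
| Patients | 20 | 0.3 | 6.70 | 44.9% |

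**Step 2: simulation of the model as worded.** There are 56 teams, yes/no adoption and no true effect, with a linear model on group and baseline adoption. Baseline is the person's own answer for staff. For patients it is the team mean, with different patients at the two times. Team effects at the two times correlate 0.5, as do a staff member's own deviations. There were 4,000 runs per staff row and 1,500 per patient row. The last column uses team-robust standard errors.

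| Model | m | ICC | Independent errors | Team-robust |
|---|---|---|---|---|
| Staff | 2 | 0.1 | 6.3% | 5.6% |
| Staff | 2 | 0.3 | 7.0% | 5.5% |
| Staff | 2 | 0.5 | 9.1% | 5.2% |
| Patients | 5 | 0.1 | 8.1% | 5.3% |
| Patients | 10 | 0.1 | 12.1% | 6.5% |
| Patients | 20 | 0.05 | 12.3% | 5.5% |
| Patients | 20 | 0.1 | 17.7% | 5.7% |
| Patients | 20 | 0.3 | 33.3% | 5.4% |

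The simulation error of one rate is √[p(1 − p)/runs]: about 0.4 percentage points at 6.3% and 1.2 at 33.3%.

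**Step 3: why the two tables differ.** The simulated ICC lies on the underlying continuous scale. Cut at the midpoint, the ICC of the yes/no answers is (2/π) × arcsin(ICC), which turns 0.3 into 0.194 and 0.5 into 0.333.

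- Staff, ICC 0.5: DE = 1 + 0.333 = 1.333, error 9.0%, against 9.1% simulated.
- Patients, m = 20, ICC 0.3: DE = 1 + 19 × 0.194 ≈ 4.69, error about 36.5%, against 33.3% simulated.

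So most of the drop from 44.9% to 33.3% comes from the scale of the ICC. Baseline adjustment removes only a little of the inflation. The mildest patient case, m = 5 and ICC 0.05, was not among the simulated rows. On this scale it gives DE = 1 + 4 × 0.032 ≈ 1.13 and an error of about 6.5%.

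**Step 4: physicians.** There is one respondent per team, so m = 1 and DE = 1. Team clustering does not affect that model.

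**The case against.** The strongest reply is that the article never says the models are individual-level or that errors are independent. It gives no regression family, unit of analysis or variance method. It condenses a longer protocol, to which such details are commonly left, and the authors plainly know GEE. The patient model even points the other way: outpatients surveyed at baseline and follow-up are presumably mostly different people, so baseline adoption would have to be defined above the patient. A team-level analysis would remove the problem.

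Much of this stands. A reader might infer that the authors have chosen an independence model; the text does not support that, so the point has to be conditional. A reader might also infer that false claims of a toolkit effect would run at 45%. That figure is the extreme corner of two assumed ranges, takes no account of the baseline covariate, and presupposes a 5% test that the article does not state for adoption. For staff, the only perspective with a documented cluster size, the inflation is modest.

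Nor is it certain that the physician team is the assigned unit. Assignment partly follows the structure of the physician–staff relationship, the aim #2 Measures section speaks of sites in the toolkit group, and staff may serve several physicians.

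What does not stand is that this is only a detail left out. The article fixes the covariates, the separate models and the coefficient to be reported for a primary outcome. It names a correlated-data method for the aim #2 associations and none for the comparison in which assignment itself is clustered.

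**Conclusion.** The concern holds in conditional form. As worded, the staff and patient adoption models carry no stated allowance for clustering, although assignment is by group of staff. If fitted to individual respondents, which the individual surveys and the separate models by perspective suggest but do not prove, they understate the standard error of the group coefficient for any positive within-cluster correlation.

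With baseline adjustment and the assumed ICCs, a nominal 5% test runs at about 6–9% for staff and at about 8–33% in the simulated patient scenarios. The direction is certain once the ICC is positive. The size is not, because it depends on ICCs and a number of surveyed patients that the article does not give. The patient models carry most of the risk.

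**What to change.** State the unit of analysis and fit the staff and patient adoption models with clustering at the unit actually assigned. That is the physician team, or the practice or site if staff are shared between physicians or assignment followed sites. Any of three routes will do:

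- the GEE already planned for aim #2, with a small-sample correction;
- a mixed model with a random effect for that unit;
- an analysis of unit-level summaries.

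For patients, define the baseline adoption measure at the same unit level. If the unit turns out to be the site, only six are available; unit-level summaries are then safer than GEE, and the physician model needs the same treatment.

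The cost is a sentence or two in the aim #1 Analysis section and wider intervals for the adoption effect. In the simulations above, team-robust standard errors brought the error rate to 5.2–5.6% for staff and 5.3–6.5% for patients.
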